### Statistical analysis

All allocated subjects will be analyzed with the available data, i.e. on the basis of the intention-to-treat (ITT). A significance level of 95% (two sided p-values alpha < 0.05) will be used. After examining the data for normality (Kolmogorov-Smirnov test) the outcome measures will be analyzed using ANOVA (assuming normal distribution) or Kruskal-Wallis (non-parametric). Demographic characteristics and other baseline values will be described using descriptive statistics for each group. Significant group interactions will be analyzed post-hoc. We will use the Bonferroni method to appropriately adjust the overall level of significance for multiple outcomes.

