**Method/Design:**

A randomized controlled trial of 2 × 2 factorial design will be conducted in the Rehabilitation Hospital Affiliated to Fujian University of Traditional Chinese Medicine. A total of 240 patients with cognitive dysfunction after stroke who meet the eligibility criteria will be recruited and randomized into RehaCom training group, acupuncture group, a combination of both or control group in a 1:1:1:1 ratio. All patients will receive conventional treatment. The interventions will last for 12 weeks (30 min per day, Monday to Friday every week). Evaluations will be conducted by blinded assessors at baseline and again at 4, 8 and 12 weeks. Outcome measurements include mini–mental state examination (MMSE), Montreal cognitive assessments (MoCA), functional independence measure scale (FIM) and adverse events.

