As mentioned above, the acupuncture focus on the global cognitive function from the holistic conception of TCM, while the RehaCom cognitive training concerns the specific impaired cognitive functions which need to be trained from the viewpoint of symptomatic treatment. However, the cognitive impairment after stroke is so complexity that one single treatment cannot resolve effectively. Due to the limited efficacy of the interventions separately used and the growing interest in recovery from post-stroke cognitive dysfunction has led to development of multiple therapeutic strategies for cognitive rehabilitation, that is, the remediation or alleviation of cognitive deficits resulting from neurological damage [36]. As the two interventions which can treat the cognitive impairment from global cognitive function to specific impaired cognitive function, we firmly believe that the interaction of multiple therapeutic strategies (the combination of acupuncture and RehaCom cognitive training) to produce an effect greater than simply the sum of the individual effects of each intervention if they were used separately. Besides, the effects of acupuncture and RehaCom cognitive training have not been systematically compared, nor has the possibility of a synergistic effect of combination of the two therapeutic modalities been evaluated.

Nonetheless, after reviewing a great amount of literature, we found that few studies had addressed these questions. So it is still unclear whether this form of intervention (acupuncture combined with RehaCom cognitive training) can be considered as a treatment of choice. Though, a current systematic review [37] showed that acupuncture in combination with other therapies could significantly improve cognitive functions. Besides, acupuncture would be a useful tool in conjunction with RehaCom from our preliminary clinical practice. However, convincing evidence is still inadequate. Therefore, we designed a randomized controlled trial of 2 × 2 factorial design to address these problems and hopefully provide a more conclusive answer to the questions. We hypothesized that the synergistic effect of acupuncture and RehaCom cognitive training is greater than simply the sum of the individual effects of each intervention if they were used separately; and the acupuncture or RehaCom cognitive training significantly improves cognitive outcomes, or to a similar extent, assessed after the intervention, compared to the control group.

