In this trial, our first aim is to evaluate the synergistic effect of acupuncture and RehaCom cognitive training on cognitive dysfunction after stroke. Our second aim is to determine whether acupuncture and RehaCom cognitive training, alone or in combination, are more effective than conventional treatment on the rehabilitation of post-stroke cognitive dysfunction. The work reported in this article is financed by the Program of International S&T Cooperation (No. 2011DFG33240), Ministry of Science and Technology of the People’s Republic of China.

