### Blinding

Blinding of study personnel in research projects is a main quality criterion of a study [43]. Nevertheless, blinding of therapists in an intervention study who perform experimental treatment in patients is not always feasible, especially if experimental intervention shall be combined with in the therapy. Consequently, hiding the patient’s allocation in this setting will not be possible. Therefore, neither therapists nor patients will be blinded in this study. We will assign a specified RA to be in charge of the management of the random allocation sequence and blind code of allocation in which the intervention group (CG, EG1, EG2, EG3) will be replaced by the alphabet A, B, C or D. In this trial, we will assign each investigators a well-defined obligation: the research assistant and treating therapists (acupuncturist) will be not involve in the assessment of outcomes; The outcome assessors and the statistic analyzer will be not involved in the participants’ screening and allocating. The blind code will be disclosed after the statistical analysis is completed.

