## Discussion

The study is a single-blind, randomized controlled trial of 2 × 2 factorial design mainly to evaluate the synergistic effect of acupuncture and RehaCom cognitive training in patients with cognitive disorders caused by stroke. The trial is sponsored and financially supported by the Program of International Science and Technology Cooperation (No. 2011DFG33240), which is the most important projects to promote national S&T innovation capabilities based on international cooperation.

Cognitive impairment is a condition characterized by mental deficits. Up to 75% of stroke survivors may be considered to have cognitive impairment [8]. These disorders severely limit individual autonomy for successful reintegration into family, work and social life [4]. Despite a high prevalence of post-stroke cognitive impairment, therapeutic possibilities are still limited. So far, complementary or alternative therapies seem to have some positive effect in the post-stroke cognitive impairment (e.g. acupuncture [17, 40] and computer based cognitive training [56]). But, improvements in cognitive function tend to be modest. Besides, currently there is not enough evidence for acupuncture [57] or computer-assisted cognitive training [56] based on strict clinical trial of evidence-based medicine (EBM) because of the poor quality of current studies, for example, small sample size, no description of methods for randomization, no standardized acupuncture protocol, no strict quality control which may lead to performance bias, and so on.

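### If the normality test rejects, the plan switches to Kruskal-Wallis, which cannot test synergy, and it does not say whether the ANOVA alternative is factorial

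*Protocol article*

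**What the plan says.** All references are to the protocol article.

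- **Aim.** Background: "our first aim is to evaluate the synergistic effect of acupuncture and RehaCom cognitive training on cognitive dysfunction after stroke". The hypothesis there is an effect "greater than simply the sum of the individual effects of each intervention if they were used separately". The Discussion again describes the trial as designed "mainly to evaluate the synergistic effect of acupuncture and RehaCom cognitive training in patients with cognitive disorders caused by stroke".
- **Design.** Abstract, Method/Design: patients are "randomized into RehaCom training group, acupuncture group, a combination of both or control group in a 1:1:1:1 ratio".
- **Test.** Statistical analysis: "After examining the data for normality (Kolmogorov-Smirnov test", and then "the outcome measures will be analyzed using ANOVA (assuming normal distribution) or Kruskal-Wallis (non-parametric". The two factors, a product term and a synergy contrast are not named.
- **Interaction.** The same section mentions it once: "Significant group interactions will be analyzed post-hoc".
- **Sizing.** Sample size treats the trial as a comparison of k = 4 groups. It assumes mean MMSE improvements of 2.7 (CG), 5.9 (EG1), 3.7 (EG2) and 6.0 (EG3), SD 5.2, two-group labels aside, with α 0.05 and 90% power, and arrives at about 50 per group.
- **Masking.** Blinding replaces the arms by letters A to D. "The blind code will be disclosed after the statistical analysis is completed".

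**The concern.** Super-additivity is one specific contrast of the four arm means: EG3 − EG1 − EG2 + CG > 0. A test of whether the four arms differ at all is a different question, and it can be answered yes because RehaCom alone works.

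The plan lets a normality test on the trial's own data choose the analysis. One of the two possible choices cannot address the first aim, and the other is described too briefly to tell whether it does. The trial could therefore report a significant four-group result without having tested its primary hypothesis. Pairwise comparisons after Kruskal-Wallis would not repair this, since none of them tests additivity.

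**Working it through.** **Inputs** (Sample size): means CG 2.7, EG1 5.9, EG2 3.7, EG3 6.0; σ = 5.2; k = 4; α = 0.05; 90% power; about 50 per group. The formula itself is not in the text at hand, so its form is inferred.

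**1. Reproduce the plan's figure.** Grand mean = 18.3/4 = 4.575. Sum of squared deviations = 3.5156 + 1.7556 + 0.7656 + 2.0306 = 8.0675. For a four-group omnibus ANOVA the non-centrality is λ = n × 8.0675/5.2². Noncentral F power is 89.7% at n = 48, 90.3% at 49 and 91.0% at 50. The tabulated version, n = ψ²σ²/[8.0675/3] with ψ from 2.17 to 2.20, gives 47.3 to 48.7. So about 50 per group reproduces as a four-group omnibus test.

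**2. What that omnibus test measures.** Split the 8.0675:
- RehaCom main effect: (5.9 + 6.0)/2 − (2.7 + 3.7)/2 = 2.75; 2.75² = 7.5625
- Acupuncture main effect: (3.7 + 6.0)/2 − (2.7 + 5.9)/2 = 0.55; 0.55² = 0.3025
- Interaction: 6.0 − 5.9 − 3.7 + 2.7 = −0.9; 0.9²/4 = 0.2025

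The interaction supplies 0.2025/8.0675 = 2.5% of the between-group variation.

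**3. Four-group test against interaction contrast.** Simulated trials, normal data, 50 per arm, SD 5.2. Exactly additive means set EG3 = 2.7 + 3.2 + 1.0 = 6.9.

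| Means (CG/EG1/EG2/EG3) | Trials | One-way ANOVA significant | Kruskal-Wallis significant | Interaction significant |
|---|---|---|---|---|
| 2.7/5.9/3.7/6.9 (no synergy) | 4,000 | 97.7% | 97.0% | 5.1% |
| 2.7/5.9/2.7/5.9 (acupuncture inert) | 2,000 | not run | 95.8% | 4.3% |
| 2.7/5.9/3.7/6.0 (protocol) | 4,000 | 90.5% | 89.1% | 9.9% |

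**4. Power of the interaction contrast.** SE = σ√(4/n) = 5.2 × √(4/50) = 1.47, so a 95% CI is about ± 1.96 × 1.47 = ± 2.9 points. With a true value of −0.9, two-sided power is 9.3% at 50 per arm and 10.2% at 60. The chance of a significant result in the direction of synergy is about 0.5%. The interaction detectable with 90% power is (1.96 + 1.2816) × 1.47 = 4.8 points at 50 per arm. Detecting 0.9 with 90% power needs 4 × (5.2 × 3.2416/0.9)², about 1,404 per arm.

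**5. How often the normality test would reject.** The documents give neither the Kolmogorov-Smirnov variant, nor the data it is applied to, nor the baseline MMSE distribution. The baselines below are assumptions.
- Uncorrected test: about 2% for integer-rounded change scores; 15% for final scores capped at 30 (baseline mean 17, SD 4).
- Lilliefors (parameters estimated), change scores: about 60 to 65% when the four arms are pooled, about 20% on model residuals.
- Lilliefors, final scores capped at 30: 96% pooled at baseline 17 (SD 4). On residuals, 16 to 27% at baseline 12 to 15 (SD 3 to 4), 63% at 17 (SD 4) and 99% at 19 (SD 4).

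No single rate can be claimed from this range.

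**The case against.** **ANOVA may already be factorial.** The text never says one-way. Study design and setting defines the arms by presence or absence of each intervention, for which a two-way ANOVA with an interaction is an ordinary reading. Reproducing the sample size shows how the trial was sized, not which ANOVA will be run, and a full plan may settle it. This stands: k = 4 and the pairing with Kruskal-Wallis suggest a one-way comparison but do not prove it.

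**A reader might infer that the interaction is relegated to post-hoc analysis.** The sentence can equally mean that an interaction already found significant is followed up with further comparisons. The documents do not support the harsher reading.

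**A reader might infer that MMSE, an integer scale capped at 30, will usually fail the normality test.** That depends on the test variant, the score and an undocumented baseline.

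**A reader might infer that the A to D masking prevents the test.** Four letters can be split into two pairs in only three ways. All three contrasts can be computed under code and labelled at unmasking. Masking is an inconvenience only.

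**A four-group comparison has a use.** It serves the second aim, each treatment alone or combined against conventional treatment, and nothing says that an omnibus result will be reported as synergy. This is also fair.

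None of this rescues the Kruskal-Wallis branch. The article states that test, so this is not detail left out for brevity.

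**Conclusion.** The point holds in this form. On the Kruskal-Wallis branch the first aim has no stated test, under any reading of the rest of the section. On the ANOVA branch the interaction test is unstated rather than shown to be absent.

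The distinction matters because, under additive means with SD 5.2, normal data and 50 per arm, a four-group test is significant in about 97% of trials and the interaction contrast in 5%. How often the fallback would be used is unknown: about 2 to 15% with the uncorrected test, and from roughly 20% to over 90% with Lilliefors, under assumed baselines.

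It would go too far to say that the plan certainly contains no interaction test, or that the normality test will usually fail.

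**What to change.** Name one primary analysis: a linear model for week-12 MMSE, adjusted for baseline MMSE, with acupuncture (yes/no), RehaCom (yes/no) and their product. The product term is the primary estimand, reported with its 95% CI whatever its p-value.

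- Remove the normality-test switch to Kruskal-Wallis. If residuals look non-normal, keep the same model with robust or bootstrap standard errors.
- Keep four-group or pairwise comparisons for the second aim.
- As a convenience, give the masked analyst the pairing {CG, EG3} versus {EG1, EG2}, or compute all three two-versus-two contrasts under code and label them at unmasking.
- State that the 90% power in Sample size was not derived for this test. Under the protocol's own means the interaction is −0.9 and unadjusted two-sided power is about 9% at 50 per arm. Baseline adjustment may narrow the interval, but the documents give no correlation from which to say by how much.

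The cost is one paragraph of analysis text and a masking note. Baseline MMSE is already collected, so no new data are needed. The real cost is candour: the primary test will be imprecise at the planned size.

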**Flow diagram of participants.**

### Sample size

We use the improvement of MMSE scores as the main effect indicators to estimate the sample size. Sample size calculations are performed to determine the number of participants needed to detect effect sizes. Based on the similar papers reported before [38–40] and our preliminary data indicates the mean with SD of the MMSE scores were μ1 = 2.7, μ2 = 5.9, μ3 = 3.7, μ4 = 6 in the CG, EG1, EG2, EG3 respectively, with the SD *σ* = 5.2. To detect 4.6 mean differences among the groups at end of interventions, k represents of the number of groups which is 4 in this trial. About 50 individuals per group will be calculated according to the formula:

With a type I error of 5% (α = 0.05) and 90% power (β = 0.10). Estimating a 20% dropout rate during the study, a minimum of 240 total participants is needed to reach the target 60 participants per group.

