### Outcome assessment

This study will run for 12 weeks and cognitive function will be assessed by neuropsychological measurement scales which include Mini–mental state examination (MMSE), Montreal Cognitive Assessment (MoCA), Functional Independence Measure Scale (FIM) at baseline and again at 4, 8 and 12 weeks (within a time window: +/- 3 days). All outcomes will be measured by several experienced assessors who are blinded to the randomization group after the baseline visit in the Evaluation Department of Rehabilitation Hospital Affiliated to FJTCM.

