### Primary outcomes

#### Mini–mental state examination (MMSE)

The mini–mental state examination (MMSE) or Folstein test [49] is a brief 30-point questionnaire test that is used to screen for cognitive impairment. MMSE includes items to evaluate spatial and temporal orientation, short-term memory, attention and calculation abilities, language, thinking, and action planning. MMSE will take about 15 to 20 minutes. In this study we use the Chinese version of MMSE [42] to follow the course of cognitive changes in an individual over time, thus making it an effective way to document an individual’s response to treatment.

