### Quality control

A trained RA will explain to each participant the nature of the study, its purpose, the procedures involved, the expected duration, the potential risks and benefits and any discomfort it may entail. Patients or their legal guardians will receive an information letter about the study and there will be no time limit for them to consider implications, ask questions, and respond to the invitation to participate. Participants will be informed that they are free to withdraw from the treatment under study at any stage for any reason without any consequences.The participants screening must according to the inclusion and exclusion criteria. If they meet the inclusion criteria and not meet the exclusion criteria, this procedure will pass. On the contrary, the disqualified participants will be excluded, and the researchers will record the number and the reasons.The random allocation sequence will be produced by an independent statistician via the statistical software SAS 9.1. The project manager allocates the participants according to the random allocation sequence, and it must be deposited for safe keeping ensuring nobody else knows. The cessation of blinding will take place only after all the trial is completed.The missing data should not appear in the CRFs of the missing data in principle. If any missing data appears, researchers should find out whether it is missed in the raw data. If it is missed when loading into database, it should be reloaded. If the missing data affects outcome measure, the participant will be rejected.To ensure that treatments are of a high standard and delivered in accordance with the trial protocol, clinicians involved in assessments, treatment or training will have to provide proven record of at least three year of clinical experience and certified training or education in related fields of rehabilitation or research. The needling will only be performed by professional physicians with specific training in TCM and a minimum of five years of experience. They will participate in a two-day training in the standard operating procedures (SOPs) provided by the author of the manualized protocol and the standard operation videos. In this training the protocol will be explained and practiced on each other during exercises and role-plays. The therapist in the control condition will receive no extra training. In addition, all treatments provided to patients will be carefully recorded in the CRFs.Blinding of study personnel in research projects is a main quality criterion of a study [43]. Although patients, investigators, and therapists administering treatment will not be blinded, those assessing the patients for primary and secondary endpoints will be blinded to patient treatment assignment. The investigators, therapists and assessors are different people. Patients will be told not to talk to the examiner about the group allocation or therapy content during the post-intervention assessments.To maintain the quality of this trial, monitoring will be conducted by the PL located in the Rehabilitation Hospital Affiliated to FJTCM. Investigators can also be convened to discuss practical issues that might be encountered, such as dealing with serious adverse events, revising the protocol, and addressing certain important issues that might be raised by investigators and participants.

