Besides, the cognitive impairment after stroke is so complexity that one single treatment cannot resolve effectively. Additionally, the effects of acupuncture and RehaCom cognitive training have not been systematically compared, nor has the possibility of a synergistic effect of combination of the two therapeutic modalities been evaluated. Due to the acupuncture focus on the global cognitive function from the holistic conception of TCM, while the RehaCom cognitive training concerns the specific impaired cognitive functions which need to be trained from the viewpoint of symptomatic treatment. So, we believe that the interaction of multiple therapeutic strategies (the combination of acupuncture and RehaCom cognitive training) to produce an effect greater than simply the sum of the individual effects of each intervention if they were used separately. Nonetheless, the convincing evidence is still lacking. Therefore, our trial aims to clarify these issues and hopefully provide a more conclusive answer to the questions by the means of randomized factorial controlled trial.

We used cognitive abilities screening scales includes MMSE, MoCA and FIM as the outcome measures in order to track changes in the functional status over the 12-week interventions period. The MMSE [49] is a global measure of cognitive function that has been used extensively both as a diagnostic tool for dementia screening as well as a cognitive outcome measure for gauging the efficacy of the cognitive alterations, for example [58, 59].The MoCA was designed as a rapid screening instrument for mild cognitive dysfunction, which has been found to have high sensitivity and specify for the detection of mild cognitive impairments in various neurological disorders (e.g. Stroke [60]). The FIM was designed to assess disability based on the International Classification of Function (ICF). It is a useful measure of physical and cognitive disabilities in patients with AD and VaD which may reflect global cognitive function [54]. Therefore, they can be a comprehensive neuropsychological test battery to monitor the general cognitive alterations which can reach a more reliable conclusion.

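### The named tests make no use of the week 4 and week 8 scores, so outcome-related dropout that differs across the 2×2 cells could bias the week-12 interaction; a likelihood repeated-measures model, without the rejection rule, is the better choice

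*Protocol article*

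**What the plan says.** MMSE, MoCA and FIM are scored "at baseline and again at 4, 8 and 12 weeks (within a time window: +/- 3 days" (Outcome assessment; Table 1 lists the same rounds). The reason given is longitudinal. The MMSE is used "to follow the course of cognitive changes in an individual over time", and the Discussion says the scales were chosen "in order to track changes in the functional status over the 12-week interventions period".

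On analysis, the Statistical analysis section says "the outcome measures will be analyzed using ANOVA (assuming normal distribution) or Kruskal-Wallis (non-parametric". It names no visit, no time factor and no within-patient correlation. The analysis set is defined by "All allocated subjects will be analyzed with the available data, i.e. on the basis of the intention-to-treat (ITT". Quality control adds a different rule: "If the missing data affects outcome measure, the participant will be rejected".

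Sample size bases the calculation on MMSE improvement in four groups at the end of the interventions and allows for attrition: "Estimating a 20% dropout rate during the study, a minimum of 240 total participants is needed to reach the target 60 participants per group". Blinding states that patients and therapists are not blinded. The first aim, in Background, is synergy, which in a 2×2 design is the interaction.

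**The concern.** A between-group test on available week-12 scores uses only patients who reach week 12. A patient who leaves after week 4 or week 8 has already shown how he or she was doing, and that information is discarded. This is harmless if dropout is unrelated to outcome. If it is related, the remaining patients no longer represent the arm.

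The interaction is EG3 − EG1 − EG2 + CG. Suppose poor improvers leave and raise the observed mean of an arm by b. If this happens in CG only, the interaction shifts by +b, which is apparent synergy, and each active-versus-control difference shrinks by b. If it happens equally in the three active arms only, the shift is b − b − b = −b, and real synergy is masked. If it happens equally in all four arms, the shift is b − b − b + b = 0. What matters is therefore whether the selection is non-additive across the cells. Patients here know their arm, so reasons for leaving could differ by arm, and the quantity at risk is the trial's first aim.

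**Working it through.** **1. Reproducing the plan's own figure.** Inputs from Sample size: mean improvements CG 2.7, EG1 5.9, EG2 3.7, EG3 6.0; SD 5.2; α = 0.05; power 90%; k = 4.

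- Grand mean: 18.3/4 = 4.575.
- Sum of squared deviations: 3.516 + 1.756 + 0.766 + 2.031 = 8.0675.
- One-way ANOVA with noncentrality n × 8.0675/5.2²: n = 49 per group for 90% power; power is 0.910 at n = 50 and 0.897 at n = 48.

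The stated figure of about 50 is thus a one-way, four-group comparison at one time point. Weeks 4 and 8 play no part in it.

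**2. Scale of the interaction.**

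- Implied by the planning means: 6.0 − 5.9 − 3.7 + 2.7 = −0.9.
- Evaluable per arm after 20% dropout: 60 × 0.8 = 48.
- Standard error: 2 × 5.2/√48 = 1.50.

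**3. Bias when dropout depends on observed scores.** The document gives no arm-specific dropout and no within-patient correlation, so these are assumptions: 60 per arm, true interaction 0, correlation 0.5 and 0.7 between visits, and a logistic dropout slope of 1 per SD (2 in one row). Low improvers leave, and rates are in the order CG/EG1/EG2/EG3. Cells show the results at correlation 0.5 / 0.7.

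| Pattern | Bias, available week-12 data | Bias, likelihood model | False-positive rate, available data |
|---|---|---|---|
| CG informative, others random, 20% each | +0.52 / +0.71 | 0.02 / 0.04 | 6.3% / 7.9% |
| 35/15/15/15% | +0.52 / +0.72 | 0.04 / 0.06 | 6.6% / 8.0% |
| 35/15/15/15%, slope 2 | +0.67 / +0.96 | 0.01 / 0.03 | 7.9% / 10.3% |
| 15/15/15/35% | +0.45 / +0.64 | −0.04 / −0.04 | 6.8% / 7.1% |
| 10/30/30/10% | −0.91 / −1.32 | 0.04 / −0.01 | 9.4% / 14.7% |

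A second simulation used the planning means, change SDs of 4.2, 4.8 and 5.2 at weeks 4, 8 and 12, adjacent-visit correlation 0.6 to 0.8 and dropout of 20–25%. It gave +0.53 to +0.76 for informative dropout in CG only and −0.59 to −0.77 in the active arms only. The likelihood estimate was within 0.03.

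**4. When there is no bias.** With informative dropout in all four arms (about 24%), the available-data interaction bias was between −0.06 and +0.07. With uneven but additive rates (30/20/20/10%) it was about zero by either method.

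**5. When the model does not fully correct.** If dropout depends on the unseen score, the CG-informative pattern leaves 0.49 of 0.76 at correlation 0.5 and 0.32 of 0.81 at 0.7. The 10/30/30/10% pattern leaves 0.99 of 1.47 and 0.66 of 1.58. Roughly 40% to 65% of the bias remains.

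**6. Precision.** With uninformative dropout the standard error falls from 1.521 to 1.486 (2.3%) or from 1.537 to 1.461 (4.9%). That is a minor gain; bias is the main reason to change.

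**The case against.** **The single time point is an inference.** The Statistical analysis section does not say that the tests are run at one visit, and ANOVA could mean repeated-measures ANOVA. This stands as a caution. The inference is still reasonable: ANOVA is paired with Kruskal-Wallis, which compares independent groups, and the sample size reproduces as a one-way comparison at the end of treatment. Classical repeated-measures ANOVA would also drop incomplete patients, so that reading does not solve the problem.

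**Model detail belongs in the SAP, which is not shown.** Covariance structure and visit terms could indeed wait for it. But the article does fix the test family, the analysis set and the rejection rule, and the point rests on these rather than on silence.

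**The scenarios are chosen.** The documents give 20% dropout with no split by arm, and nothing shows that selection will differ between cells. This stands. A reader might infer that uneven dropout by itself creates or hides synergy. It does not: the dropout must be related to outcome and non-additive across the cells.

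**A reader might also infer that a repeated-measures model would simply correct the bias.** The near-zero bias in step 3 follows from letting dropout depend on observed scores only. Step 5 shows what remains otherwise.

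**Nor can it be taken as settled that controls get no extra session and so have a special reason to leave.** Table 2 suggests this, but Study design and setting says that all groups have the same 30 minutes of intervention. The argument needs only that patients know their arm.

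**Conclusion.** The point holds in limited form. The tests as named leave the week 4 and week 8 scores out of the week-12 comparison, and a better method exists for data the trial already plans to collect. If outcome-related dropout differs non-additively across the cells, the MMSE interaction could be off by roughly 0.5 to 0.9 points, and by up to 1.3 in the harsher pattern with excess dropout in both single-treatment arms. That is about one-third to three-fifths of its standard error (0.5/1.5 to 0.9/1.5), and as large at the upper end as the interaction implied by the planning means. The effect on the false-positive rate is moderate: about 6% to 10% in most patterns, and 14.7% at worst in the table.

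These sizes rest on assumed correlations, dropout slopes and arm-specific patterns that the document does not supply. With similar selection in every arm the bias is about zero. The change is worth making before the data are analysed, but the documents do not show that the result will be biased.

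**What to change.** 1. In Statistical analysis, replace ANOVA/Kruskal-Wallis for each scale with a likelihood-based mixed model for repeated measures on all observed scores. Include acupuncture, RehaCom, their product, visit and the interactions of these terms with visit, with an unstructured within-patient covariance.
2. State that the primary contrast is the week-12 acupuncture × RehaCom interaction on MMSE change from baseline. The time course can be read from the same model.
3. In Quality control, delete the rule that rejects a participant whose missing data affect the outcome. It conflicts with the commitment to analyse all allocated subjects and would remove the partial records the model needs, so item 1 cannot work while it stands.
4. Add a sensitivity analysis for dropout that depends on unseen scores, with departures allowed to differ by arm, since departures that are additive across the cells cancel in the interaction.

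The cost is a change of wording and a little more analysis work. No extra patients, visits or measurements are needed. The model still makes an assumption, but a weaker one than the completely random dropout on which an available-data week-12 comparison generally relies.
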